### Statistical analysis

Data coding and analysis will be conducted using the IBM SPSS Statistics v.21 software program. Primary outcome measures will be examined both with intention-to-treat analyses and analyses conducted on treatment completers. For the efficacy hypotheses, paired t-tests and linear mixed models will be used to investigate changes in pre versus post primary and secondary outcome measures. Statistical significance will be considered as *P <*0.05. The mixed model approach has been selected as it allows for inter-participant and intra-participant variance as well as the inclusion of participants with missing data, whilst maintaining power.

In accordance with the protocol of Forman *et al*. [70], mechanism of change hypotheses will be examined using correlation and independent t-tests to determine which variables to include in a multivariate analysis of variance. Post-hoc multiple comparisons (for example, Bonferroni correction) will be performed to determine where significant differences lie. Multivariate regression examining factors related to treatment success will also be employed and will include examining any demographic (such as age, gender, family functioning) and clinical (such as pre-scores, psychological flexibility) factors that might be related to outcomes. Mediational analysis, a regression-based approach, will be used to test hypotheses about the mechanisms behind outcome, as this is a powerful way of determining mechanisms by which an effect operates rather than the existence of an effect [73]. It allows for more than one mediator and adjusts all paths for the potential influence of covariates not proposed to be mediators in the model. Receiver operating curve plots of the true positive and false positive rate for different possible cut-points of the regression test will be conducted because receiver operating curves convey information relating to the trade-off between sensitivity and specificity, and maximize predictive value. The coordinates of the receiver operating curve will be used to determine the optimal cut-point for the test. The full information maximum likelihood method will be used to deal with missing data.

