#### Randomization

Following baseline assessment, eligible participants and their caregivers will be randomized to one of three conditions - ACT, CBT or a waitlist control group - for a period of 10 weeks (described in detail below). Each group will comprise up to eight children/adolescents as well as their caregivers. The researchers involved in this study are six registered psychologists, all trained in ACT and CBT. This will be a block randomized controlled trial, with the participant serving as the unit of randomization. Randomization will be undertaken via a publically available random assignment software application, ‘Graphpad’ [http://www.graphpad.com/quickcalcs/].

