#### Intervention

Participants allocated to ACT or CBT groups will complete a group-based therapy program of 10 × 1.5 hour sessions of the applicable treatment at CHW, which will be provided at no cost. Up to eight children or adolescents will be involved in each group program. Treatment will be conducted by between two and four psychologists, dependent upon final group numbers. All psychologists involved in the delivery of the intervention have been equally trained in both ACT and CBT, with the exception of one who has advanced training in CBT and intermediate training in ACT.

Caregivers will be involved concurrently in a “parent-as-coach” manner. Across both programs, the treatment will incorporate aspects that involve the participants and caregivers working independently of one another, as well as aspects that require working together. Both programs will also require regular completion of between-session practice tasks by both caregiver and the participant that will be reviewed at the subsequent session.

Both ACT [60-62] and CBT [63-65] programs will be based upon treatment manuals, tailored to the needs of participants. Manuals have been developed for children, adolescents, caregivers and therapists. Each program incorporates a series of psychological techniques consistent with the therapeutic modality employed. However, there are some commonalities across both interventions including psychoeducation, skills training and exposure. Although exposure to feared situations is a prominent technique employed across both ACT and CBT, the approach differs across therapies. In CBT, the focus is on challenging maladaptive thinking to enable performance of the exposure behavior, whereas in ACT, children or adolescents are encouraged to attempt to alter the relationship they have with their anxiety by distancing themselves from it and increasing their willingness to experience it.

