### Treatment fidelity

Across the group treatment period, all psychologists will receive weekly group supervision. As the psychologists involved in the delivery of the treatment are involved in the delivery of both the ACT and CBT treatments, treatment fidelity is an important consideration that will be addressed via video-recording a subset of each 10 week program. Video-recording will be conducted with the consent of all participants and will be reviewed and analyzed by an independent assessor, for fidelity with the identified treatment (ACT or CBT) in accordance with a checklist designed for this study. The independent assessor will be a psychologist, with training in the use of both ACT and CBT, within the Department of Psychological Medicine who is not involved in the treatment groups. Two independent assessors will be employed to ensure reliability of treatment fidelity ratings. Feedback on the outcome of these reviews will be provided back to the research team and subsequently explored within weekly supervision. In line with the protocol of Forman *et al*. [70], therapist allegiance towards treatment will be assessed by having each psychologist respond to the question ‘Which treatment do you think leads to better outcomes, ACT or CBT?’. Therapist allegiance will be examined as a variable of interest in terms of any possible association with study outcomes.

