Although some studies have found monetary incentives facilitated increased recruitment and retention in research with adolescents [74], this has not been observed universally [75,76] and will not be feasible in the current study. Instead, engagement in the research will be supported by the provision of the treatment by registered psychologists experienced in the delivery of these programs at no cost and ensuring expectations of participants is communicated with clarity and consistency, particularly in the early stages of recruitment. Retention issues will also be addressed by enabling participants in the intervention groups to complete a ‘catch-up’ session the following week if they are unable to attend a session with one of the treating psychologists and encouragement of in-group socialization within the therapy to establish group cohesiveness. It is anticipated that these approaches will be somewhat supportive in addressing recruitment and retention issues in the current trial.

The researchers will publish outcomes of this trial in peer-reviewed clinical journals. Findings will also be disseminated at relevant conferences that would be attended by practicing clinicians. Findings will also be presented at CHW in-service days as well as for various community organizations in the Area Health Service, and school counselors can inform parents, increase community awareness and refer clinicians to the program.

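### ACT and CBT are delivered in therapy groups of up to eight, but neither the stated efficacy analysis nor the sample size accounts for clustering by therapy group

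*Protocol article*

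**What the plan says.** - **Delivery** (protocol article, Intervention): "Participants allocated to ACT or CBT groups will complete a group-based therapy program of 10 × 1.5 hour sessions". "Up to eight children or adolescents will be involved in each group program". On staffing: "Treatment will be conducted by between two and four psychologists, dependent upon final group numbers".
- **Unit of randomization** (Randomization): "This will be a block randomized controlled trial, with the participant serving as the unit of randomization".
- **Interaction within groups** (Discussion): one of the retention measures is "encouragement of in-group socialization within the therapy to establish group cohesiveness".
- **Controls** (Controls; Follow-up assessment): waitlist participants receive no group treatment until after their 10-week assessment.
- **Analysis** (Statistical analysis): paired t-tests and linear mixed models for pre-post change, at P<0.05. The stated reason for the mixed model is that "The mixed model approach has been selected as it allows for inter-participant and intra-participant variance", together with its handling of missing data.
- **Sample size** (Sample size calculation): at least 30 per arm for power 0.8 at an effect size of 0.6 to 0.7. No ICC or inflation factor is given.
- **Therapists** (Treatment fidelity): "the psychologists involved in the delivery of the treatment are involved in the delivery of both the ACT and CBT treatments". Therapist allegiance will be examined for association with outcome, which does not adjust standard errors for clustering.

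**The concern.** Ten weeks of shared sessions, the same leaders and deliberately fostered cohesion make it plausible that members of one therapy group end up more alike than members of different groups. That correlation arises after randomization and exists only in the treated arms, so the design is partially nested. A random effect for the participant handles repeated measures on one person. It does nothing for correlation between people in the same group, and a paired t-test ignores it too.

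ACT versus CBT is most exposed, because both sides of the contrast are clustered. A two-sided test would reject too often. If the hypothesis that ACT is no worse than CBT is read as non-inferiority, intervals that are too narrow also make a false non-inferiority claim more likely. The information in the trial is also less than a count of participants suggests.

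**Working it through.** **Inputs from the article.** Group size m: at most 8. Total 150 (90 children, 60 adolescents). Sample size 30 per arm, power 0.8, effect size 0.6–0.7, P<0.05.

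**Assumptions.** Equal allocation, so about 50 per arm (30 children, 20 adolescents). With at most eight per group this needs 4 child and 3 adolescent groups, 7 per active arm, mean size 50/7 = 7.1. ICC 0.01 to 0.10, all specific to the therapy group. Continuous outcome, two-sided tests.

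**Step 1: the plan's own figure.** A two-sample t-test at power 0.8 needs 44.6, 38.1 and 33.0 per arm (two-sided) or 35.0, 30.0 and 25.9 (one-sided) for effect sizes 0.60, 0.65 and 0.70. The stated 30 is matched by a one-sided test at 0.65. It is also matched by a two-sided ANCOVA at 0.70 with an assumed baseline correlation of 0.3, and nearly by a three-arm ANOVA with one arm differing by 0.70 (30.5). All of these treat participants as independent.

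**Step 2: type I error.** The design effect is DE = 1 + (m − 1) × ICC. The actual level is 2 × [1 − Φ(1.96/√DE)] for ACT versus CBT. For ACT versus waitlist, where only one arm is clustered, DE is replaced by (1 + DE)/2. With m = 7.1:

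| ICC | DE | ACT v CBT | ACT v waitlist |
|---|---|---|---|
| 0.01 | 1.06 | 0.057 | 0.053 |
| 0.02 | 1.12 | 0.064 | 0.057 |
| 0.05 | 1.31 | 0.087 | 0.068 |
| 0.10 | 1.61 | 0.123 | 0.087 |

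Simulation of participant-level t-tests with seven groups of 6 to 8 per active arm agrees to within 0.005. At ICC 0 it returns the nominal 0.05. Simulating pre-post change (pre-post correlation 0.5, group effect at post only) gives 0.058, 0.089 and 0.125 for ACT versus CBT at ICC 0.01, 0.05 and 0.10. Allowing for within-person correlation therefore does not remove the inflation.

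**Step 3: power, ACT versus CBT, effect size 0.6, ICC 0.05.** Effective n = n/DE, two-sided t-test:

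| n per arm | Independent | m = 6 (DE 1.25) | m = 8 (DE 1.35) |
|---|---|---|---|
| 50 | 0.84 | n = 40.0: 0.76 | n = 37.0: 0.72 |
| 30 | 0.63 | n = 24.0: 0.53 | n = 22.2: 0.50 |

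These figures ignore the further small loss from having few groups, and so few degrees of freedom.

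**Step 4: effect of shared therapists.** If half of the ICC is a therapist effect matched across ACT and CBT, simulated ACT–CBT type I error at ICC 0.02, 0.05 and 0.10 is 0.056, 0.064 and 0.083. If all of it is matched, the error is at or below 0.05. The article does not give the share.

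**The case against.** **The article does not say the model excludes therapy group.** A reader might infer that the mixed model allows for participant-level variance and nothing else. The sentence gives a reason for choosing the method. It is not a full list of random effects, and an unseen analysis plan could add a group term. This limits certainty but does not remove the point: the article names two variance levels, omits the one its delivery creates, pairs the model with a test that also ignores it, and fixes a sample size that assumes independence.

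**Shared therapists need not inflate ACT versus CBT.** A reader might count common therapists as a further source of inflation. Because the same psychologists deliver both treatments, their effects are largely crossed with arm and may partly cancel, as Step 4 shows. Therapy groups remain nested within arm, so group-specific effects do not cancel.

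**Caregivers are not shared.** Each young person attends with his or her own caregiver. Caregivers are only present together in the group.

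**Eight is a ceiling and the ICC is unknown.** Both are true, hence the ranges. At ICC 0.01 the inflation is slight, and at zero there is none.

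**Clustering does not explain the whole power gap.** A reader might attribute the shortfall at 30 per arm to it. At effect size 0.6, two-sided power is already 0.63 under independence against the stated 0.80. That gap of 0.17 is a separate matter; at ICC 0.05 clustering takes a further 0.10 to 0.13.

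**The outcomes differ from the calculation.** The primary outcomes include diagnosis and shifts between severity ranges, while the figures here use a continuous score, as the plan's effect-size calculation does. The direction is the same for a binary outcome; the exact sizes would differ.

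**Conclusion.** The point holds. For any positive group-specific ICC, the analysis as described gives standard errors that are too small, chiefly for ACT versus CBT. Over the assumed ICC range and at about 50 per arm, the inflation runs from slight at the low end to more than double the nominal level for ACT versus CBT at the high end; ACT versus waitlist stays below 0.09. The loss of power at ICC 0.05 is about 0.08 to 0.13. For ACT versus CBT these are upper figures for each ICC, since they treat all clustering as group-specific. The results rest on an assumed ICC, equal allocation, and groups of six to eight. The documents do not support saying that a group term is ruled out, or that clustering is the main reason why 30 per arm falls short.

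**What to change.** 1. Record a therapy-group identifier for every treated participant.
2. Add a random intercept for therapy group in the ACT and CBT arms, pooled over the child and adolescent strata, with waitlist participants as singletons (a partially nested model) and Satterthwaite degrees of freedom. The term must act on the post-treatment outcomes, for example with baseline as a covariate; a group effect constant over time would drop out of a pre-post contrast.
3. Keep the term even if its estimated variance is small.
4. Base between-arm conclusions on this model and not on paired t-tests.
5. Report the ICC.
6. Restate power at the planned sample size over a range of ICC and group size. No additional enrolment is asked for.

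**Cost.** One extra variable and one extra term in a model already planned. Confidence intervals become somewhat wider, and the group variance is estimated from few groups (about 14 in all), so it will be imprecise. Pooling over age strata and the small-sample degrees of freedom are there for that reason.

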**Methods/design:**

We will recruit 150 young people (90 children and 60 adolescents) diagnosed with an anxiety disorder and their parent or caregiver. After completion of baseline assessment, participants will be randomized to one of three conditions (Acceptance and Commitment Therapy, Cognitive Behavior Therapy or waitlist control). Those in the Acceptance and Commitment Therapy and Cognitive Behavior Therapy groups will receive 10 × 1.5 hour weekly group-therapy sessions using a manualized treatment program, in accordance with the relevant therapy, to be delivered by psychologists. Controls will receive the Cognitive Behavior Therapy program after 10 weeks waitlisted. Repeated measures will be taken immediately post-therapy and at three months after therapy cessation.

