## Methods

### Study design

This is a prospective randomized controlled trial. It is a three (group: two intervention and one control) by three (time: pre-, immediate post- and three-month post-treatment) repeated measures factorial design. The overall study design is illustrated in Figure 1.

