### Sample size calculation

A power analysis was conducted to determine the approximate sample size required to achieve an examination of the effectiveness of a manualized ACT group-therapy program, the most sensitive aim. At a power level of 0.8, with an effect size (ES) of 0.6 to 0.7, it is estimated that a minimum 30 participants in each group is required to detect a significant difference between each of the three groups. The employment of analysis of covariance and mixed model statistical tests for pre versus post comparisons will also offer increased power to detect significant differences. The estimated ES of 0.6 to 0.7 is based on the results of three previous meta-analyses of ACT. In terms of primary outcome measures, Hayes *et al*. [31] observed that, compared to structured interventions, ACT was superior after treatment (*d* = 0.48) and at follow-up (*d* = 0.63). Ost [71] found that ACT was superior to established treatments achieving a mean ES of 0.68. In contrast, Powers *et al*. [72] found that, on primary outcome measures, ACT achieved ES in the range *g* = 0.42 to 0.68 when ACT was compared with control or waitlist conditions and *g* = 0.18 compared to established treatments. The ES for the current study is estimated in line with the higher-end ES results achieved across the aforementioned meta-analyses. The rationale for this is that these meta-analyses have incorporated studies for a range of low-prevalence disorders - disorders that are typically considered to be treatment resistant - whereas the current study focuses only on anxiety, high prevalent disorders, widely acknowledged to be more responsive to treatment.

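### The screening t-tests and MANOVA on the adolescent process measures name no baseline covariate, so if they compare randomised arms they give up precision that the pre-treatment scores could supply

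*Protocol article*

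**What the plan says.** The secondary aim concerns adolescents only. It is examined with five process instruments: AFQ-Y, CAMM-20, PANAS-X, TAS-20 and VLQ (protocol article, Process measures and Table 2). The Statistical analysis section states that "mechanism of change hypotheses will be examined using correlation and independent t-tests to determine which variables to include in a multivariate analysis of variance", with post-hoc multiple comparisons to follow. It does not say which groups the t-tests compare, whether post or change scores are tested, or whether any covariate enters.

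Two other analyses appear in the same paragraph. One is a regression on treatment success that examines "clinical (such as pre-scores, psychological flexibility) factors that might be related to outcomes". The other is a mediation analysis, which is the step said to test the mechanism hypotheses. It is described as adjusting its paths for covariates that are not themselves proposed mediators, but those covariates are not listed.

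The Study design section describes a "three (time: pre-, immediate post- and three-month post-treatment) repeated measures factorial design". The Initial assessment section describes a baseline questionnaire battery without naming its scales. The Sample size calculation section credits ANCOVA and mixed models for pre versus post comparisons with extra power, in the context of the effectiveness aim.

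**The concern.** A t-test and a MANOVA, as named, do not use the baseline value of the measure being compared. The mechanism hypotheses are framed as decreases in avoidance and fusion and increases in awareness, acceptance and valued living, so pre-treatment process scores are needed anyway and should be available.

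The mechanism aim also has the smaller sample: 60 of the 150 participants, or about 20 per arm. The t-tests decide which variables go forward to the MANOVA. A process measure that therapy truly changes can therefore be dropped at that step for want of precision, when data already collected would have supplied some of it.

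**Working it through.** **The plan's own figure.** The only power statement is for the effectiveness aim: "At a power level of 0.8, with an effect size (ES) of 0.6 to 0.7", it gives "a minimum 30 participants in each group is required to detect a significant difference between each of the three groups". For a two-sided pairwise comparison, n per group = 2 × (1.960 + 0.842)² / d². This gives 44 at d = 0.6 and 33 at d = 0.7, so 30 is not reproduced over the stated range. A one-sided test at d = 0.65 does give 30. That is a separate matter and neither supports nor weakens this point. No power is stated for the mechanism analysis, so there is no figure of the plan's to reproduce here.

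**Inputs**
- Significance level: "Statistical significance will be considered as *P <*0.05". Sidedness is not stated; two-sided is assumed.
- Sample: "We will recruit 150 young people (90 children and 60 adolescents". With three arms and equal allocation among adolescents (ratio not stated), 60 / 3 = 20 per arm.
- Effect size d: 0.6 to 0.7, borrowed from the efficacy calculation because none is given for the process measures.
- Correlation r between pre- and post-treatment score: not given. A range of 0.3 to 0.7 is shown.
- Equal SDs before and after treatment, and no dropout.

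**Method.** Each power figure comes from a noncentral t distribution with noncentrality d* × √(20/2), where d* is the effective standardised difference:
- post score: d* = d, 38 df
- change score: d* = d / √(2(1 − r)), 38 df
- ANCOVA: d* = d / √(1 − r²), 37 df

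Example at d = 0.6 and r = 0.5. The post and change scores both have d* = 0.60, because 2(1 − 0.5) = 1. ANCOVA has d* = 0.6 / √0.75 = 0.693. Power is 0.456 for the unadjusted tests and 0.569 for ANCOVA, a difference of 11.3 points.

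| d | r | Post | Change | ANCOVA | Loss against post | Loss against change |
|---|---|---|---|---|---|---|
| 0.6 | 0.3 | 0.456 | 0.346 | 0.491 | 3.5 | 14.5 |
| 0.6 | 0.5 | 0.456 | 0.456 | 0.569 | 11.3 | 11.3 |
| 0.6 | 0.7 | 0.456 | 0.665 | 0.735 | 27.9 | 6.9 |
| 0.7 | 0.3 | 0.578 | 0.446 | 0.618 | 4.0 | 17.2 |
| 0.7 | 0.5 | 0.578 | 0.578 | 0.702 | 12.3 | 12.3 |
| 0.7 | 0.7 | 0.578 | 0.795 | 0.855 | 27.7 | 6.0 |

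Losses are in percentage points, taken from unrounded powers. A normal approximation gives nearly the same differences (27 to 28 points against post scores at r = 0.7).

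**What this means for screening.** If a variable goes forward only when its t-test is significant at 5%, then at d = 0.6 and r = 0.5 a truly affected scale is missed 1 − 0.456 = 54% of the time unadjusted, and 1 − 0.569 = 43% adjusted.

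**The case against.** The strongest objection is that the t-tests only select variables and that mediation, which can carry covariates, tests the hypotheses. A reader might infer that the whole mechanism analysis ignores baseline. The text does not support that: pre-scores enter the regression, and baseline scores are not excluded from the mediation model. But neither analysis commits to adjusting a process measure's arm contrast for its own baseline. The regression concerns treatment success, and the mediation covariates are left open.

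Second, the article does not say what is compared. A t-test takes two groups and the trial has three arms. Treatment successes against failures is a possible reading, and the MANOVA could have time as a factor. The step also follows a cited protocol that may settle this. The objection stands as a condition on the point. Randomised arms remain the natural reading, because the post-hoc comparisons are meant to locate differences between groups.

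Third, a reader might take 11 to 12 points as the established loss. It is the result at r = 0.5 only, and it also needs the borrowed effect size and equal allocation.

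Fourth, it is tempting to say that chance baseline imbalance biases the contrasts. With 20 per arm the baseline difference has a standard error of √(2/20) = 0.32 SD, so on any one scale a difference above 0.3 SD has a 34% chance. Randomisation nevertheless leaves the unadjusted comparison unbiased with its type I error intact, and that variation is already in its standard error. The 34% restates the loss of precision and is not a second harm.

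Finally, baseline collection of each process scale is inferred from the design and the direction of the hypotheses. It is not stated scale by scale.

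**Conclusion.** The point holds as one of efficiency, for the screening t-tests and the MANOVA, on the condition that they compare randomised arms. Adjustment beat both post and change scores at every correlation examined. How much it gains depends on a correlation the protocol does not give: about 4 to 28 points of power over post scores, and about 17 down to 6 over change scores, as r goes from 0.3 to 0.7. These figures rest on 20 adolescents per arm, a two-sided 5% test and an effect size of 0.6 to 0.7 taken from the efficacy aim. The article does not support a claim of bias, of inflated type I error, or of a mechanism analysis with no baseline adjustment anywhere. This is a free or cheap improvement for the secondary aim.

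**What to change.** In the Statistical analysis section, state that between-arm comparisons of process measures use ANCOVA with arm and the same measure's pre-treatment score. Use MANCOVA with the baseline process scores for the joint test, or a mixed model that adjusts for baseline in the same way. State which groups are compared. In the mediation model, include each mediator's baseline score as a covariate.

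The cost is wording plus about one error degree of freedom per covariate, so up to about five in a joint test if each of the five instruments contributes one score. No new data, visits or staff are needed, provided the process scales are in the baseline battery as the design implies.
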